### Sample size calculation

It is assumed that the proposed new intervention would be implemented and funded across the NHS only if it achieved at least a medium sized effect. An effect size of 0.35 is equivalent to an improvement of satisfaction ratings on the MANSA of at least one scale point (on a 7-point scale) for 4 out of a total of 12 life domains. An improvement of quality of life in four life domains is usually regarded as a meaningful difference to patients’ life.^16^

For detecting such an effect size with 90% power, assuming a conservative intraclass correlation coefficient (ICC) of 0.07 for patients treated by the same professional in the intervention group, 229 patients in the intervention group and 229 in the control group will be required (total sample=458). A 1:1 allocation ratio has been chosen for organisational ease. This requires eight additional patients to be recruited compared with the absolute minimum required sample size with slightly uneven groups. A drop-out rate (from the study) at 6 months follow-up of 20% (in line with recent trials of similar interventions with the same patient group) (VOLUME trial) was assumed.^18^ The sample size calculation was based on 10 patients being treated and followed-up per clinician on average. Based on recruiting 12 patients per clinician the final total sample size target was 576 patients (288 per arm). Recruitment and intervention delivery to SCENE were paused during the COVID-19 pandemic making a study extension necessary (see the section Impact of the COVID-19 pandemic). For this a sample size recalculation was conducted using values observed so far for two quantities. The drop-out rate was inflated from 20% to 25% (actual rate to date 24%). Cluster size in the intervention arm was reduced from 10 to 3 patients per treating professional on average allowing for observed variability in patients per professional. Using these estimates the updated total number of patients to recruit is 504.

### Qualitative process evaluation

A qualitative process evaluation will be conducted, employing semistructured interviews with a number of purposively selected patients and social coaches. Interviews will be transcribed and analysed using thematic analysis.^28^

We will interview 40 patients in the experimental group to explore experiences of the intervention and descriptions of qualitative changes in their social network, contacts and activities. A topic guide for interviews was developed with input from the LEAP. Interviews will be conducted after the end of the 6-month outcome assessment, so that the interviews do not interfere with the effects of the intervention in influencing the primary outcome (quality of life at 6 months). Unblinded researchers will identify participants, conduct the interviews and manage qualitative data, so researchers assessing outcomes remain blind to allocation.

We will use purposive sampling, to include patients who differ according to gender, whether they live in urban or rural settings and whether or not they completed the intervention. Sampling of social coaches will include those who have seen more than three patients and those who have seen fewer.

### Adherence to manual

Adherence to manual will be assessed through our adherence checklist. Routine documentation and audiotapes of patient–professional meetings (for consenting participants) will be compared against the clinician-reported adherence schedule to check reliability. This is a self-reported checklist of whether and how the different steps of the intervention (box 2) are addressed. Clinicians will have addressed all the eight steps of the intervention and conducted at least three sessions with a given patient for the intervention to be deemed as completed.

### Economic evaluation

The within trial analysis will adopt the NHS and Personal Social Services perspective to assess the cost-effectiveness of the psychosocial intervention for patients with psychosis compared with best standard practice.^29^ The evaluation will focus on the 18 months from baseline until the end of the follow-up period. The analysis will adhere to guidelines for good economic evaluation practice as outlined in Ramsey *et al*^30^ and Sanders *et al.*^31^

Resource-use associated with delivery of the interventions in both trial arms will be identified using a specially designed intervention implementation form. Participants’ use of health services, including mental health and hospital care, will be extracted from the NHS Digital database. All participants will be asked to complete a modified version of the Client Services Receipt Inventory to obtain information about their of other psychosocial interventions, medication and receipt of informal care from families and friends. The quantities of all resource use will be combined with unit costs to generate cost at the individual participant level. Unit costs will be obtained from various sources, including a specially designed coach demographics questionnaire, NHS Reference costs,^32^ Unit Costs of Health and Social Care,^33^ NHS drug Tariff^34^ and the UK earnings data.^35^

As for outcomes, the primary outcome measure for the economic evaluation will be collected using the EQ-5D-5L instrument.^23^ We will calculate the participant-level quality-adjusted life-years (QALYs) and use the EQ-5D-5L data with the area-under-the-curve approach.^36^ The secondary outcome will be measured using the MANSA. The time points for collecting costs and outcome data are reported in table 1.

Both costs and outcomes occurring during the last 6 months of the follow-up period will be discounted at 3.5% in line with the NICE recommendation.^29^ Costs and outcome data will be analysed by treatment allocation, and differences between trial arms will be estimated over 18 months, adjusting for baseline differences using regression analysis. We will select an appropriate method to handle missing data based on the nature of our data.

Cost–utility analysis and cost-effectiveness analysis will be applied in the economic evaluation. In the cost–utility analysis, the estimates of incremental cost-effectiveness ratio (ICER) for the psychosocial intervention compared with best standard practice will be presented against the decision-maker’s willingness to pay a value of £20 000–£30 000 per QALY.^23^ To report the uncertainty of the point estimate of ICER, we will use the non-parametric bootstrap approach to estimate the CI around the ICER. We will also present the probability that the intervention is cost-effective against a range of decision makers’ willingness to pay value using the cost effectiveness acceptability curve. In the cost-effectiveness analysis, we will calculate the incremental cost per unit change on the MANSA scale and uncertainty surrounding the ratio.

A number of sensitivity analyses to assess the impact of key assumptions as well as uncertainty with key parameters in the economic evaluation will be conducted to (1) explore the impact of alternative assumptions about the missing data mechanism; (2) consider uncertainty in the most important cost drivers to assess the impact of healthcare use; (3) use a broader analytical perspective by including additional costs for informal care; (4) use 0–6 months from randomisation as the time period for economic evaluation.

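### The planned bootstrap confidence interval for the ICER cannot be read if the QALY difference is near zero; a net-benefit interval from the same replicates should replace it (minor)

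*Protocol article*

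**What the plan says.** All of this is in the protocol article, under Economic evaluation.

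- **Denominator of the ratio.** "We will calculate the participant-level quality-adjusted life-years (QALYs) and use the EQ-5D-5L data with the area-under-the-curve approach".
- **Horizon and adjustment.** "differences between trial arms will be estimated over 18 months, adjusting for baseline differences using regression analysis".
- **Benchmark.** The ICER is set against a "willingness to pay a value of £20 000–£30 000 per QALY".
- **First uncertainty summary.** "To report the uncertainty of the point estimate of ICER, we will use the non-parametric bootstrap approach to estimate the CI around the ICER".
- **Second uncertainty summary (the acceptability curve).** "We will also present the probability that the intervention is cost-effective against a range of decision makers’ willingness to pay value using the cost effectiveness".
- **Second ratio.** For cost per MANSA unit: "we will calculate the incremental cost per unit change on the MANSA scale and uncertainty surrounding the ratio". No interval method is named for it.

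Net monetary benefit, the cost-effectiveness plane, and the handling of replicates with a zero or negative QALY difference are not mentioned. Cost-effectiveness is listed among the Secondary objectives.

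**The concern.** An ICER has an ordered meaning only while the QALY difference keeps one sign. A negative ratio arises when the intervention is cheaper and better, and also when it is dearer and worse. A positive ratio arises when it is dearer and better, and also when it is cheaper and worse. As the QALY difference approaches zero the ratio grows without limit and changes sign. If the bootstrap distribution of the QALY difference covers zero, sorting the ratios and reading off limits ranks values that have no order.

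Nothing in the article places the QALY difference clear of zero. The Sample size calculation section powers the trial on MANSA ("An effect size of 0.35 is equivalent to an improvement of satisfaction ratings on the MANSA of at least one scale point"), and the primary endpoint is at 6 months. The ICER rests on EQ-5D-5L QALYs over 18 months, for which no target difference is given. The control group also receives an intervention (the information booklet). At stake is whether the interval printed beside the ICER can be interpreted.

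**Working it through.** **The plan's own figure.** The article states no QALY difference, cost difference or ICER, so only the sample size can be reproduced. For a partially nested design, n per arm = (1.960 + 1.282)² × (1 + DE) / d². Here d = 0.35, ICC = 0.07, mean cluster size is 3, and two-sided alpha of 0.05 is assumed.

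- Equal clusters: DE = 1 + 2 × 0.07 = 1.14, so n = 183.6, rounded up to 184. Then 184 / 0.75 gives 246 per arm, or 492 in total.
- Cluster-size CV of 0.5 (assumed): DE = 1 + (1.25 × 3 − 1) × 0.07 = 1.1925, so n = 188.1, rounded up to 189. Then 189 / 0.75 = 252 per arm, or 504 in total, the stated figure.

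**Analysed per arm.** 504 × 0.75 / 2 = 189. The 25% loss is the 6-month rate.

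**Assumptions not in the documents.** 18-month QALY SD 0.2, 0.3 or 0.4; cost SD £8000; true cost difference £500; independent normal draws (200,000) standing in for the bootstrap distribution; percentile limits for the ratio.

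**Share of replicates with no QALY gain.** SE = SD × √(2/189) = 0.0206, 0.0309 and 0.0411. The share is Φ(−gain / SE). For example, with SD 0.3 and gain 0.02, Φ(−0.02 / 0.0309) = 0.26.

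| True gain (QALY) | SD 0.2 | SD 0.3 | SD 0.4 |
|---|---|---|---|
| 0 | 50% | 50% | 50% |
| 0.01 | 31% | 37% | 40% |
| 0.02 | 17% | 26% | 31% |
| 0.03 | 7% | 17% | 23% |
| 0.05 | 0.8% | 5% | 11% |
| 0.10 | <0.1% | 0.1% | 0.8% |

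**What the negative ratios contain (SD 0.3, gain 0.02).** Cost SE = 8000 × √(2/189) = £823. About 19% of draws are dominated (dearer and worse) and 20% dominant (cheaper and better). Both appear as negative ICERs.

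**ICER interval against net-benefit interval, gain 0.02.**

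| SD | 95% percentile limits, ICER (£ per QALY) | Width | 95% limits, net benefit at £20 000 (£) | Width |
|---|---|---|---|---|
| 0.2 | −352,000 to +386,000 | 739,000 | −1906 to +1705 | 3611 |
| 0.3 | −310,000 to +339,000 | 649,000 | −2130 to +1911 | 4041 |
| 0.4 | −264,000 to +272,000 | 536,000 | −2371 to +2177 | 4548 |

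As the QALY data become noisier, the ICER interval narrows, so its width does not measure precision here. The net-benefit interval widens, as it should.

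**Closed-form check (SD 0.3).**

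- At £20 000: mean = 20 000 × 0.02 − 500 = −£100; SE = √[(20 000 × 0.0309)² + 823²] ≈ £1029; limits about −£2116 to +£1916, which agrees with the simulation. The probability of positive net benefit is Φ(−100 / 1029) = 0.46, which is the value the acceptability curve would show at that threshold.
- At £30 000: mean = £100; SE ≈ £1239; limits about −£2330 to +£2530.

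**Where the problem fades.** At a gain of 0.10 the ICER limits are about −£12,000 to +£24,000 (SD 0.2) and −£16,000 to +£38,000 (SD 0.4). Almost every negative draw is then dominant, and a negative lower limit can be read as such.

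**The case against.** The strongest reply is that a reader might infer that decision makers are left with nothing but an uninterpretable interval. The article does not support that. Its next sentence commits to an acceptability curve, which at each threshold is the probability of positive net benefit and holds in all four quadrants. This stands and limits the point. What the curve does not give is the size and precision of the net benefit, and the ICER interval is the summary the plan assigns to the point estimate.

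Secondly, the article says non-parametric bootstrap, not percentile limits, and a full analysis plan may say how replicates in different quadrants are treated. That cannot be seen here. The concern rests on the stated choice to put an interval on the ratio, not on the missing handling rule. The percentile limits above are an illustration.

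Thirdly, the size depends on assumed inputs and on results not yet known. This also stands. Adjustment for baseline could lower the effective SD: moving from 0.3 to 0.2 takes the share at a gain of 0.02 from 26% to 17%. Loss by 18 months above 25% would push the other way: at 176 per arm the range at that gain is 17–32%.

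Two wider readings are not supported:

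- **MANSA ratio.** A reader might extend the point to cost per MANSA unit, but no interval is fixed for it. The trial has 90% power for its 6-month MANSA effect; if that effect holds, the expected z is about 1.96 + 1.28 = 3.24, and hardly any replicates at that time point would cross zero.
- **Clustering.** A reader might infer that clinician clustering is ignored in the economic analysis. The article says only "adjusting for baseline differences using regression analysis", and silence in a condensed article is not an error. If the ICC of 0.07 and cluster size of 3 applied to QALYs and costs, the SE would rise by about √[(1 + 1.14) / 2] − 1 = 3.4%.

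**Conclusion.** The concern holds in a limited form. The plan fixes a confidence interval on a ratio that loses its order when the QALY differences straddle zero, and the design does not guard against that. With 189 analysed per arm and an assumed QALY SD of 0.2 to 0.4, about 17–31% of replicates fall at or below zero for a true gain of 0.02, 1–11% for 0.05 and under 1% for 0.10. The QALY SD, cost SD and cost difference are assumptions throughout. For small gains the ICER limits would be unreadable; for gains near 0.10 they would be usable.

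Severity is minor. One of two planned uncertainty summaries for a secondary objective is affected. The acceptability curve, the point estimates and the primary clinical analysis are untouched, so it would be wrong to conclude that the economic evaluation as a whole is unsound.

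**What to change.** In the Economic evaluation section, or in the health-economics part of the analysis plan:

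1. Replace the interval for the ICER with incremental net monetary benefit and its bootstrap confidence interval at £20 000 and £30 000 per QALY, the article's own thresholds.
2. Show the replicates on the cost-effectiveness plane.
3. Keep the acceptability curve as planned.
4. Report the ICER as a point estimate only, and state dominant or dominated where that applies.

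The same bootstrap replicates serve for all four, so no new data are needed and the cost is a change of wording. The downside is that readers who expect an interval around the ICER will not find one; a sentence giving the reason would answer them.

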### Ethics and dissemination

The study was reviewed and a favourable opinion received from the London Hampstead NHS Research Ethics Committee (19/LO/0088). Any serious adverse events are recorded in specific forms and their relationship with the intervention are adjudicated by site leads who are all senior clinicians. Written informed consent is provided by participants after discussion with researchers. A model consent form is enclosed as a online supplemental document.

10.1136/bmjopen-2021-050627.supp1Supplementary data

Any personal information stored in locked cabinets on NHS premises if in paper version, and encrypted if in electronic version. Dataset will be accessed by the study team and after the primary analysis may be made available to other parties subject to data sharing agreements.

Throughout all phases of the research, we will disseminate information about the activities of the programme through social media and a project specific website (http://scene.elft.nhs.uk/) in order to reach a wider public audience. Authorship guidelines for outputs will follow the International Committee of Medical Journal Editors (ICMJE) guidelines.

When results become available, they will be disseminated through:

Scientific publications in peer-reviewed open-access journals.Presentations at national and international conferences and to professional and non-professional audiences at appropriate events.Existing networks, including but not limited to the WHO, the benchmarking network in mental health, organisations involved in Quality Improvement programmes and the professional networks of the programme management group members.

### Impact of the COVID-19 pandemic

Following the outbreak of COVID-19 in the UK, recruitment was stopped from 16 March 2020 to 1 October 2020. We decided to stop the intervention delivery from 16 March 2020 to 21 August 2020 in accordance with social distancing guidelines at that time.

We added an additional follow-up at 10 months from randomisation for those participants who had already been randomised when the study was stopped, but had not completed the treatment period. A sensitivity analysis will consider end-of-treatment as the outcome of comparison, and hence include the assessment of quality of life at 10 months from randomisation rather than at 6 months for these participants.

We created additional adapted versions (used separately from the standard ones) of the SCA and of the Time Use Survey and data collected will be analysed to capture online social contacts and activities throughout the trial.

The recruitment and randomisation of participants was resumed on 1 October 2020. Additional instructions to social coaches were provided on physical distancing with patients and on how to encourage social activities which are either online or can be carried in accordance with different scenarios and different physical distancing directives.

Research follow-up of participants at different timepoints was never stopped and continued over the phone or via videoconferencing.

We have calculated that 70 participants may have been especially affected by the COVID-19 pandemic in that their primary outcome was assessed at a time when restrictions meant that they could not meet more than one person outside of their household.

To adjust for any pandemic effects on the intervention itself, the outcomes or both, a sensitivity analysis will adopt a mixed-effects model approach, grouping participants according to the physical distancing guidance that they have been exposed to. Individual treatment effect estimates of participant groups with different levels of exposure will be calculated.

## Discussion

This study addresses a gap in mental healthcare provision, that is, the lack of treatments available to help patients overcome their social isolation.^4^ It has broad inclusion criteria and is carried out across a large number of urban, semiurban and rural sites. This will allow to control by design a number of patient-level (eg, financial and clinical status) and area-level characteristics (eg, availability of affordable activities, distance and travel required to access them) which might influence intervention effectiveness. The active control condition, that is, the provision of comprehensive information on local social activities, does not only control for service attention to social activity and information provision, but also arguably represents a reflection of best current practice.

The methodological choices made when designing the study come with some limitations:

Older people and those who are not fluent in the language of their country of residence encounter additional barriers to socialisation. Hence, we restricted inclusion criteria to patients with psychotic disorders of working age and to those who are fluent in English, to limit heterogeneity of our sample. Future trials and/or implementation studies should target these populations specifically.The new intervention has been implemented in services directly as part of the trial. Social coaches are trained but do not have previous experience in delivering this type of approach.

In addition to this, the COVID-19 outbreak meant that more of the intervention has to be delivered remotely than originally envisaged, and we do not know whether and how that will impact on outcomes. We have a sensitivity analysis to estimate this as explained in detail in the following paragraph.

If the intervention is found to be effective in increasing social contacts and improving quality of life, it can promptly become part of the therapeutic armamentarium of mental health services. The flexibility of the approach, which can be delivered by different type of professionals, might facilitate its uptake within the ever evolving landscape of mental health services. In line with the design of the trial, we do not intend for the social coach to become be a new professional role in itself. Instead, the function of social coaches can be taken on by different professionals and exercised along with other clinical activities.
